#### HIV Infant Tracking System 2.0 Intervention Specifications

Clear reporting of intervention components and implementation strategies is needed for meaningful application in practice or testing in research [40,41]. The entry point into the HITSystem 2.0 will be the first PMTCT appointment for women previously diagnosed with HIV or newly confirmed HIV positive during antenatal HIV screening. Actions include automated prompts to PMTCT providers, prompts to central laboratory technicians who process viral load (VL) samples, and SMS texts to patients driven by national algorithms for optimal PMTCT care (Table 1). Automated electronic prompts to providers will persist as Web-based dashboard alerts until addressed. Automated SMS texts are sent to HIV-positive pregnant women as cues to action; women can select the preferred content and frequency for one-way ART adherence text messages at the time of enrollment. This is one of the first interventions to target adherence support messages during pregnancy, thus texting options (content and frequency) will be informed by Phase 1 formative research, and actual preferences will be assessed by this pilot study. Community health care workers can reach out to patients who miss services and/or do not respond to SMS text messages or calls to encourage retention. The HITSystem 2.0 will integrate PMTCT and EID services through 1 coordinated system-level intervention; this will permit longitudinal follow-up of mother-infant pairs to assess PMTCT outcomes.

**Table 1 table1:** HITSystem 2.0 intervention components. Expected timing, dose, and target of alerts and SMS (short message service) texts to providers and HIV positive pregnant women.

Actors	Actions	Timing	Dose^a^	Target
Hospital-based providers; providers	Algorithm-driven electronic alerts	When PMTCT^b^ service late/missing (enrollment-infant EID^c^ link)	Avg=8 per mom, range=0 to 14+	PMTCT quality: complete PMTCT retention (pregnancy to EID link)
Lab-based providers; lab techs	Algorithm-driven electronic alerts	When receipt of VL^d^ sample or VL results delayed	Avg=1 per mom, range=0-2+	PMTCT efficiency: reduced turn-around time for key PMTCT services

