#### Viral Load Suppression

We will document the proportion of pregnant women who had a VL sample collected during pregnancy: 6 months after ART initiation for those diagnosed during ANC or within the past 6 months for those already established on ART, in accordance with national guidelines. We will abstract data on VL from the HITSystem 2.0 (intervention) and the patient file and laboratory records (control) to assess the proportion with VL tests taken, the turn-around time (TAT) for return of results, and the proportion with suppressed VL results (defined as<1000 viral copies/ml) during pregnancy.

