Using chi-square tests, we will compare the proportion of pregnant women (1) attending all scheduled PMTCT appointments (4 or more PMTCT visits and late or missed visits), (2) tested for VL (VL sample collected, results returned, and detectible VL values), (3) delivery at the hospital, (4) enrolling in EID (dried blood spot sample collected by <7 weeks), and (5) have an infant diagnosed with HIV, between intervention and control sites. The median number of PMTCT appointments, median gestational week at first PMTCT appointment, and median TAT for VL results will be calculated and compared using Mann Whitney *U* tests. Although medication adherence documentation at the control site (typically described as poor, fair, or good) will not permit direct comparison, the proportion of pregnant women at the intervention site with >95% adherence will be described. Participant preferences for the content and frequency of SMS text messages for medication adherence support will also be described. *P* values will be adjusted (using Tukey correction) for multiple tests, where appropriate. Quantitative data will be analyzed using Statistical Application Software (SAS) version 9.4.

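### Viral load turnaround time is compared only where a result came back, and the intervention acts on return, so the comparison can be biased in either direction

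*Protocol article*

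**What the plan says.** Under Viral Load Suppression, the protocol article lists among its secondary measures "the turn-around time (TAT) for return of results, and the proportion with suppressed VL results". The measure is a time to return. The data sources differ by site: "We will abstract data on VL from the HITSystem 2.0 (intervention) and the patient file and laboratory records (control").

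Under Statistical Analyses, the method is fixed: "median TAT for VL results will be calculated and compared using Mann Whitney *U* tests". The same paragraph compares the proportion of women "tested for VL (VL sample collected, results returned, and detectible VL values") by chi-square, so return of results is also an outcome in its own right. Time-to-event methods are named only for the duration of retention. No rule is given for a sample whose result is still outstanding or lost.

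Table 1, in the intervention specifications, sends electronic alerts to laboratory staff when receipt of the sample is delayed or "VL results delayed". Their stated aim is "PMTCT efficiency: reduced turn-around time for key PMTCT services". The text before the table adds: "Automated electronic prompts to providers will persist as Web-based dashboard alerts until addressed". The control hospital has no such alerts.

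**The concern.** Turnaround time has a value only for a returned result. A Mann-Whitney test on the available values therefore compares two subsets formed after the hospitals were allocated. The process that forms them, chasing delayed samples and results, is one the intervention is built to change. If return differs between hospitals, the two subsets can differ in turnaround even when the underlying turnaround is the same.

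Shorter turnaround is the named target of the laboratory alerts, so this is the direct test of whether they work. The Discussion says that findings on antenatal viral load results will help refine the system for a larger efficacy trial. A misleading turnaround result would feed into that step.

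**Working it through.** **The plan's own figures.** The article gives no figure for turnaround or return. Its only sample size concerns the primary outcome, and it reproduces: (1.960 + 0.842)² / 0.27² = 107.7, so 108. Nothing below changes it.

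**Assumed inputs (none is in the article).** True turnaround is identical at both hospitals and lognormal, with median 4.0 weeks and log-SD 0.6. Results returned: 95% at intervention, 70% at control.

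**Size of the gap, by which results are lost.** If only the fastest fraction r is returned, the observed median is the r/2 quantile of the full distribution. If only the slowest fraction r is returned, it is the 1 − r/2 quantile.

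| Results lost | Intervention median | Control median | Apparent effect |
|---|---|---|---|
| Slowest | 4 × exp(0.6 × z(0.475)) = 3.85 | 4 × exp(0.6 × z(0.35)) = 3.17 | 0.7 weeks slower |
| Unrelated to turnaround | 4.0 | 4.0 | none |
| Fastest | 4 × exp(0.6 × z(0.525)) = 4.15 | 4 × exp(0.6 × z(0.65)) = 5.04 | 0.9 weeks faster |

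Here z(0.475) = −0.063 and z(0.35) = −0.385, with the opposite signs for 0.525 and 0.65. Now let control return run from 60% to 80% and log-SD from 0.4 to 0.8:

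- Slowest lost: the intervention looks slower by 0.29 weeks (3.90 − 3.61) to 1.17 weeks (3.80 − 2.63).
- Fastest lost: it looks faster by 0.3 weeks (4.43 − 4.10) to 1.9 weeks (6.08 − 4.21).

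**Effect on the test.** Simulation with 2,000 runs per scenario, log-SD 0.7, true median 4 weeks at both hospitals, and Mann-Whitney at two-sided 0.05 on returned results only:

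| Results lost | Return (intervention vs control) | Direction of false result | 54 samples per site | 30 samples per site |
|---|---|---|---|---|
| Slowest | 95% vs 60% | slower | 81% | 52% |
| Slowest | 90% vs 70% | slower | 37% | 26% |
| At random | either | each way | 2% to 3% | about 2% |
| Fastest | 95% vs 60% | faster | 80% | 51% |
| Fastest | 90% vs 70% | faster | 37% | 27% |

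With equal return (80% at both), each direction was significant in about 2% to 6% of runs.

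**When the intervention is truly faster.** With true medians of 3 vs 4 weeks, the slowest results lost, 95% vs 60% returned and 54 samples per site, the returned-only test found the intervention faster in 1% of runs and slower in 13%.

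**Keeping unreturned results at the worst rank.** In the unequal-return scenarios with equal true turnaround, a falsely slower intervention appeared in at most 0.1% of runs. In the 3 vs 4 week scenario the intervention was found faster in 85%. This test also credits the intervention for returning more results. With equal underlying turnaround and 54 samples per site, it called the intervention faster in 4% to 16% of runs when the slowest were lost and in 44% to 90% when loss was random. It answers a question about return and speed together.

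**The case against.** The strongest case against has five parts.

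- **The test is not the defect.** Mann-Whitney is a rank test and can hold unreturned results at the worst rank. This stands: the test need not be dropped. The problem is which samples enter it.
- **The handling rule may sit in a document not shown.** The article never says returned results only, and an analysis plan could set a rule. But the article fixes both the measure ("the turn-around time (TAT) for return of results") and the test. Followed as written, they leave an unreturned sample without a value. That goes beyond an omitted detail.
- **The direction is not documented.** A reader might infer that slow control results vanish and that the bias therefore runs against the intervention. The article does not support this. It gives no return rates, no turnaround times and no account of which results are lost. Control data come from laboratory records as well as the patient file and are reviewed quarterly, so late results can still be captured. The Discussion names differences in documentation between sites, which need not depend on turnaround. Unreturned results also drop out at both hospitals.
- **The alerts do not guarantee return.** A reader might take them to persist until the result arrives, or take the chi-square on results returned to mean that the plan expects a difference. The text says only that prompts last until addressed, and comparing a proportion does not predict a difference.
- **Return is already compared separately.** That comparison would often reveal a gap: with 54 samples per site its power is 99.6% for 95% vs 60% and 75% for 90% vs 70%; with 30 it is 92% and 49%. It does not repair the turnaround median or its P value.

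**Conclusion.** The concern holds in a limited form. As written, the turnaround comparison is restricted to returned results, and the intervention targets delay in return, so the comparison can mislead. The sign depends on which results are missing: against the intervention if the slowest control results are lost, in its favour if the fastest are lost or undocumented, and no bias if loss is unrelated to turnaround. The 0.3 to 1.2 week gap illustrates the first case only. It rests on an assumed lognormal turnaround with a 4-week median, 95% return at intervention and 60% to 80% at control. If return is equal and of the same kind at both hospitals, the problem disappears.

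This is a secondary outcome. The change is worth making because it is cheap and, according to the Results section, no comparison between the hospitals has yet been run.

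**What to change.** State that turnaround is analysed over all viral load samples collected, measured from collection, by one method chosen now:

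- the proportion of samples with a result returned within a fixed number of weeks of collection; or
- Mann-Whitney with unreturned results at the worst rank; or
- Kaplan-Meier and log-rank, with unreturned results censored at a fixed time from collection or at the last record review. Delivery should not be the limit, because the time from sample to delivery varies by woman.

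Report the proportion of samples returned beside it at each hospital. The median among returned results can stay as a description, labelled as such.

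**Cost.** Mainly analysis wording. Computing turnaround already needs collection and return dates; the collection date must also be kept for samples without a result. The small downside is that the all-sample measure is no longer a simple median of returned results. One limit remains: a result that was returned but not documented at the control hospital would count as unreturned, so the laboratory records there should be checked before a result is classed that way.

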#### Study Sites and Setting

This study will be conducted in 2 government hospitals with similar provider-patient ratios and staffing structure, Kapsabet Hospital and Bungoma Hospital, both in western Kenya. Eligibility criteria for these hospitals include government funding; the current provision of PMTCT, EID, and ART services; at least one dedicated provider managing PMTCT services; and maintenance of individual-level patient files. Kapsabet Hospital serves a catchment area of approximately 91,000 people [43], has an average monthly EID volume of 10, and an average infant HIV transmission rate of 2.7% [44]. Bungoma Hospital serves a catchment area of approximately 92,412 people [43], has an average monthly EID volume of 18, and an average infant HIV transmission rate of 4.2% [44]. These hospitals serve less transient local populations, making them ideal pilot sites to adapt and modify the HITSystem 2.0 for the primary outcome of complete PMTCT retention.

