#### Medication Adherence

As VL is still not consistently collected during pregnancy, we will rely on other indicators of adherence including self-report of missed doses in the 7 days before appointment (prescribed vs taken) and pill counts conducted by relevant providers (dispensed vs returned). Adherence data will be entered in the HITSystem 2.0 at each appointment. We will calculate the proportion of patients who report >95% adherence to doses prescribed (7-day self-report) and pill count.

*Hospital delivery* will be estimated from the proportion of pregnant mothers who deliver at a health facility. Women who do not deliver at the study hospital will be contacted within 2 weeks of their estimated due date to check on their progress, document location of birth, and encourage prompt return to the facility for postpartum and postnatal care. *EID enrollment* will be measured using the proportion of HIV-exposed infants tested by 6 weeks of age (<7 weeks).

*Infant and maternal mortality* will be reported separately, noting all available data on date and cause of death. A future study will utilize a design with a longer follow-up period and larger sample size to adequately evaluate perinatal transmission of HIV.

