#### Power and Sample Size

The required sample size was calculated to compare differences in proportions of complete PMTCT retention for the intervention (p1) and control (p2). We estimated complete retention by combining available retention data from Kenya for each phase: antenatal retention (68%) [19], hospital-based deliveries (61%) [36], and postnatal retention for HIV-exposed infants within 12 weeks (54.9% [21] to 80.7% [20]; average 67%). Recognizing that these estimates do not represent cumulative risk for the same individuals, we conservatively estimate complete PMTCT at the control site to be 20%. Our EID pilot data showed that retention doubled at 9 months with retention rates as high as 94.2% [33]. Using a midrange between differences achieved from published studies and our own pilot study, we conservatively estimate complete retention of 47% for HITSystem 2.0 participants. A sample size of 108 (54 intervention and 54 control participants) is needed to achieve 80% power to detect a significant difference in the proportion of complete PMTCT retention with chi-square tests (goodness of fit test: contingency table) with an effect size of 0.27 and a 2-tailed alpha of .05. Accounting for the proportion with mobile phone utilization, and 1.5% maternal mortality [45] and 3.7% [46] perinatal mortality, we estimate n=70 eligible participants. During Phase 3 enrollment, we plan to enroll n=54 of the n=70 eligible PMTCT patients per hospital. On the basis of our initial HITSystem pilot where <1% of women declined, we anticipate high participation.

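### The Tukey correction named for the secondary tests gives no multiplicity control in a two-site comparison of many outcomes; as a minor related point, infant HIV is better described with exact intervals than chi-square tested

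*Protocol article*

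**What the plan says.** The Statistical Analyses section of the protocol article compares the intervention and control hospitals on five numbered sets of proportions by chi-square: appointment attendance, viral load testing, hospital delivery, EID enrolment and infant HIV. The last item reads "5) have an infant diagnosed with HIV, between intervention and control sites". Three medians (number of appointments, gestational week at first appointment, viral load turnaround time) are compared by Mann-Whitney U. The same paragraph then says that P "values will be adjusted (using Tukey correction) for multiple tests, where appropriate". It names no family of tests and, among these secondary comparisons, no contrast of three or more groups.

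Two other places bear on infant HIV. Study Sites and Setting says that Kapsabet "has an average monthly EID volume of 10, and an average infant HIV transmission rate of 2.7"%, and gives 4.2% for Bungoma. The secondary outcomes text, at the end of the part headed Medication Adherence, says: "A future study will utilize a design with a longer follow-up period and larger sample size to adequately evaluate perinatal transmission of HIV".

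**The concern.** Tukey's studentized-range procedure protects against error from making many pairwise comparisons among group means on a single outcome. Its inputs are the number of groups and the degrees of freedom; the number of outcomes does not enter. The multiplicity here runs the other way, with one contrast (hospital against hospital) and many outcomes. If the sentence is followed as written, the report will tell readers that the secondary P values were corrected although none has moved. That is worse than stating no correction, because unadjusted secondary results can at least be read as exploratory. The Discussion says that the findings will shape a larger efficacy trial, so the distinction matters even in a pilot.

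The smaller issue is that one listed outcome, infant HIV, is too rare at these hospitals for the named chi-square test to be a good choice.

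**Working it through.** **Group size.** The plan states no figure for the secondary tests, so its own figure to reproduce is the sample size: "A sample size of 108 (54 intervention and 54 control participants) is needed to achieve 80% power", "with an effect size of 0.27 and a 2-tailed alpha of .05". The rates are given as "we conservatively estimate complete PMTCT at the control site to be 20"% and "we conservatively estimate complete retention of 47% for HITSystem 2.0 participants".

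- Mean rate (0.47 + 0.20)/2 = 0.335.
- Without continuity correction, n per arm = [1.960·√(2·0.335·0.665) + 0.842·√(0.47·0.53 + 0.20·0.80)]² / 0.27² = 46.8, so 47.
- With continuity correction, n = (46.8/4)·[1 + √(1 + 4/(46.8·0.27))]² = 53.9, so 54.

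The stated 54 per arm is reproduced, and 54 is used below.

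**Tukey with two groups.** The adjusted P value is P(Q > |t|·√2), where Q is the studentized range for k = 2. The range of two means is the absolute difference between them, so this equals the ordinary two-sided P value.

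| Statistic | Ordinary P | Tukey P, k = 2 |
|---|---|---|
| t = 2.0, 106 df | .0481 | .0481 |
| t = 2.5, 106 df | .0140 | .0140 |
| z = 1.96 | .0500 | .0500 |

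**Size of the uncontrolled family.** The count depends on how the parentheses in Statistical Analyses are read.

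- Low count: 5 numbered proportions + 3 medians = 8.
- High count: attendance split in 3 (all visits, 4 or more, late or missed), viral load split in 3 (sample, result, value), delivery, EID and infant HIV at 1 each, giving 9, plus 3 medians = 12.
- If independent: 1 − 0.95⁸ = .337 and 1 − 0.95¹² = .460.

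The attendance items describe the same visits and the viral load items are linked, so the true figure is lower. The documents do not allow it to be computed.

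**Infant HIV, expected events per 54.**

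- Site rates: 54·0.027 = 1.46 and 54·0.042 = 2.27, total 3.73. Under no difference the expected event cell is 3.73/2 = 1.86 per arm.
- If only 67% of infants are tested (an assumption, borrowed from the postnatal retention average in Power and Sample Size): 1.0 and 1.5.
- National rates from the Introduction: 54·0.083 = 4.5 and 54·0.115 = 6.2.

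**One sparse table, 4 of 54 against 0 of 54.**

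- Pearson: 108·(4·54 − 0·50)² / (54·54·4·104) = 4.15, P = .042.
- Fisher: 2·C(54,4)/C(108,4) = 2·316,251/5,359,095 = .118.

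**Exact size at nominal .05, by binomial enumeration with 54 per arm.**

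| Common rate | Pearson | Fisher |
|---|---|---|
| 2.7% | .027 | .002 |
| 4.2% | .042 | .006 |
| 8.3% | .048 | .017 |
| 11.5% | .050 (.0495) | .022 |

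If the rate were halved from 4.2% to 2.1% (an assumption for illustration), power is about 7% with Pearson and 1% with Fisher.

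**The case against.** **Tukey may be meant for something else.** Trial Design plans retrospective data for pre-post comparison, which would make four site-by-period groups, and the regression models may include predictors with several categories. A variant for multiple endpoints, such as Tukey-Ciminera-Heyse, is also conceivable. The sentence applies only where appropriate. This is fair as far as it goes: it cannot be said that Tukey has no possible use anywhere in the study. But the sentence closes the paragraph of two-site tests, and the article ties it to none of these other uses. For the listed comparisons it either does not apply or has no effect.

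**An article condenses the plan.** Naming the family of tests, or a switch to an exact test for small cells, may be left to the analysis plan, and their absence is not the point here. The point is the method that the article positively names.

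**It is a pilot.** There is one primary outcome and no planned interim analysis of it, and adequate evaluation of transmission is deferred to a later study. That limits the weight of the point and makes exploratory reporting a natural choice. It does not make an ineffective correction correct.

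**Two stronger readings are tempting.** A reader might infer that the secondary P values are invalid. They are not: they are unadjusted, and neither argument touches the individual Mann-Whitney tests or the chi-square tests of common proportions. A reader might also infer that chi-square on infant HIV inflates false positives. The enumeration shows otherwise, since Pearson's exact size stays below .05 at every rate that the article gives. The gap between .042 and .118 comes from one chosen table and partly reflects how conservative Fisher's test is at these rates.

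**Conclusion.** The point stands on multiplicity. For the secondary comparisons as listed, the named correction leaves every P value as it was, so the claim of adjustment would be untrue. The familywise error left uncontrolled is at most about 34% to 46%. That range rests on a count of 8 to 12 tests, each at .05, and on independence, which is unrealistic for these outcomes. The fault is one of labelling and error control across outcomes.

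On infant HIV only a minor point remains. With expected event cells of about 1.9 per arm at the hospitals' own rates, the approximation can mislead in a single table and the test has almost no power. The result depends on which rates apply: the expected count is still below 5 at the lower national rate and passes it only towards the upper one. Planning a between-site test also sits awkwardly beside the article's statement that transmission needs a larger study.

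**What to change.** Replace the Tukey sentence with one of two statements:

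- Holm's procedure is applied across a named list of the secondary outcomes. The smallest P value is then compared with .05/8 = .00625 to .05/12 = .0042, depending on the length of the list.
- No adjustment is made, and the secondary outcomes are exploratory, reported as differences with 95% CIs and without claims of significance.

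If Tukey is intended for a pre-post or multi-category comparison, say so and confine it to that analysis.

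Take infant HIV out of the chi-square list and report the count and denominator at each hospital with exact 95% CIs, adding Fisher's exact test only if a P value is wanted.

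The cost is one or two sentences and no change to sample size or data collection. The price is stricter thresholds under Holm, or no secondary significance claims under the second option. The Results section says that no comparison of outcomes between the sites had been made, so on that footing the change can be made without knowledge of the results.
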